#### **Groups:**

- IFC + pelvic floor exercises (PFE) (n=17)
- PFE alone (n=17)

#### **Outcomes:**

- **IFC+PFE group:**
  - 64.7% achieved "complete response" (vs. 29.4% in PFE group) ( $p<0.05$ )
  - Reduced urinary incontinence episodes ( $p<0.05$ )

#### **Limitation:**

No significant uroflowmetry differences post-treatment (23).

### **4. Vitton et al. (2022) (18)**

#### **Study Design:**

Double-blind RCT on adults with chronic constipation.

#### **Intervention:**

- IFC (4,000 Hz, 80–160 Hz) vs. sham (8 weeks, 1 hr/day).

#### **Results:**

- Improved PAC-SYM ( $p<0.01$ ) and PAC-QOL ( $p<0.05$ ) scores.
- **No difference** in bowel motility or manometry.

### **Conclusion:**

IFC alleviates symptoms but lacks mechanistic impact.

## **5. Moore et al. (2019) (30)**

### **Study Design:**

Single-blind RCT on 33 women with functional constipation.

### **Intervention:**

- IFC (abdominal-posterior electrode placement) vs. sham (lateral placement).

### **Results:**

- 53% of IFC group achieved  $\geq 3$  spontaneous bowel movements/week (vs. 12.5% sham) ( $p<0.05$ ).
- Reduced laxative use ( $p<0.05$ ) but no PAC-SYM improvement.

### **Critique:**

Methodological limitations noted in systematic reviews.

## **Critical Synthesis**

- **Pediatric Studies:** Strong evidence for IFC in voiding dysfunction, with improvements in PVR, Qmax, and symptoms.
- **Adult Studies:** IFC improves subjective symptoms (constipation) but lacks objective urodynamic/physiological changes.
- **Gaps:** Limited adult data on IFC for urinary voiding disorders.

### **Is this project a thesis?**

It is not a thesis.

## **1. Participant Recruitment and Screening**

- **Sampling Method:** Non-probability convenience sampling after ethics approval.
- **Screening Process:**
  - Conducted by urologists at outpatient clinic.
  - Comprehensive evaluation including:

- Medical history and symptom assessment
- Neurological exam (anal tone, voluntary anal control, genital/lower limb reflexes)
- Urodynamic tests (cystometry for detrusor pressure, uroflowmetry)
- Pre-/post-void bladder ultrasound
- **Inclusion Criteria:** Patients meeting diagnostic criteria for voiding dysfunction.
- **Baseline Data Collection:**
  - 3-day voiding diary (fluid intake, voiding frequency)
  - Standard medical record documentation (urodynamics, ultrasound reports).

## 2. Randomization and Blinding

- **Randomization:**
  - Computer-generated block randomization (1:1 ratio, block size=4).
  - Stratified by age and symptom severity.
- **Blinding:**
  - **Patients:** Sham-controlled (details below).
  - **Outcome Assessor (Urologist):** Blinded to group allocation.
  - **Therapist:** Unblinded due to intervention nature.

Presenters and colleagues

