### **Randomization and Blinding**

- **Randomization:** Patients will be allocated with 1:1 ration into treatment (real IFC) or control (sham IFC) groups using computer-generated block randomization (block size = 4).
- **Blinding:**
  - **Patients:** Sham IFC will be applied for 1 minute (at perceptible but non-therapeutic intensity) to mimic active treatment. Real IFC will be applied with the strong tolerable intensity.
  - **Outcome assessor (urologist):** Blinded to group assignment.
  - **Therapist:** Unblinded due to treatment nature.
- **Allocation concealment:** Sealed opaque envelopes (prepared by an independent person) will ensure concealment until intervention begins.

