### **Statistical Analysis**

Descriptive information regarding the demographic characteristics of individuals in both groups will be given as means (standard deviations) for quantitative variables and as frequencies (percentages) for qualitative variables. For comparing of each demographic variable between the two study groups, the independent t-test for normally distributed quantitative variables and the Mann-Whitney test for non-normally distributed quantitative variables will be applied. The chi-square test will be conducted to compare qualitative variables.

The normality of the data in the study groups will be tested using the Shapiro-Wilk test. To comprehensively examine the extracted data, the following procedures will be carried out, as elaborated below.

To compare the mean of each variable in both groups before the intervention, two weeks after the intervention, and after a three-month follow-up period, the two-way repeated measures ANOVA will be employed, assuming the data are normally distributed. In the case of non-normality, a nonparametric equivalent will be used.

For the comparison of the mean of the variables between both groups at every time point (before the intervention, at two weeks after the intervention, and after a three-month follow-up), the two independent sample t-test will be used if the data is normally distributed and the Mann-Whitney test if the data is distributed non-normally.

To determine differences in the mean of the variables of both groups over the study period, the one-way repeated measures ANOVA will be used. In the presence of a statistically significant difference in the variable mean over time, the post hoc test with Bonferroni and Tukey corrections will be utilized. The data will be analyzed using SPSS version 26 software. The significance level in this study is assumed to be 5%.

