### 1. PVR:

- $H_0$ : There is no significant difference in mean PVR before and after treatment in the real IFC group.
- $H_0$ : There is no significant difference in mean PVR after treatment between the real IFC and sham IFC groups.

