#### **Sample Size Calculation Method**

Based on the study by Kajbafzadeh et al. and considering a 95% confidence level and 80% test power, the sample size was calculated as 14 participants per group (20).

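### Stratified randomisation is stated, but the per-visit t-test and Mann-Whitney comparisons ignore the strata; if these are prognostic, the tests are conservative and forgo some power

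*Protocol*

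**What the plan says.** Randomisation is described in three places in the protocol. Under Summary of Methodology and Analysis, the Study Design text gives a 1:1 allocation in blocks of four, and the Randomization and Blinding list repeats it as "computer-generated block randomization (block size = 4". Neither names a stratification factor. The later section 2. Randomization and Blinding gives the same scheme, "Computer-generated block randomization (1:1 ratio, block size=4", and adds "Stratified by age and symptom severity". It gives no age cut-point, no severity measure and no number of strata.

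The Statistical Analysis section fixes the between-group tests. For each variable over time, "the two-way repeated measures ANOVA will be employed, assuming the data are normally distributed", with a nonparametric equivalent otherwise. At each time point, "the two independent sample t-test will be used if the data is normally distributed and the Mann-Whitney test if the data is distributed non-normally". No test includes age, severity, a stratum term or any other covariate. The between-group hypotheses concern post-treatment values, for example "There is no significant difference in mean PVR after treatment between the real IFC and sham IFC groups". The sample size is 14 per group at 80% power.

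**The concern.** Stratified blocks hold the arms nearly level on the stratification factors, so between-stratum variation largely drops out of the arm difference. A test that ignores the strata still counts that variation in its error term. When the strata are related to outcome, the computed standard error therefore exceeds the true one, p-values are too large and confidence intervals too wide.

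The error runs in the conservative direction, so it creates no false-positive risk. What is at stake is efficiency in a trial of 28 women: the plan constrains the randomisation and then does not use that constraint in the comparison. ICIQ-FLUTS is where this is most likely to matter, because symptom severity is both a stated stratifier and, through that questionnaire, a primary endpoint.

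**Working it through.** **Inputs from the protocol.** Blocks of four, 1:1; 14 per group; 80% power; 5% significance level, taken as two-sided because sidedness is not stated.

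**Assumptions.** Two binary stratifiers (2×2 strata), and R², the share of outcome variance that the strata explain. The protocol gives neither, so R² is varied from 0 to 0.5.

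**The plan's own figure.** The sample size section gives no endpoint, effect or SD, so 14 cannot be strictly reproduced. The only numerical effect quoted from the reference paediatric trial, 77% versus 33% with a normalised flow pattern, gives 17 (unpooled) or 19 (pooled) per group two-sided, and 13 or 15 one-sided. For a mean, n = 2(1.96 + 0.842)²/d² = 14 gives d = √(15.70/14) = 1.06, or 1.10 with the t distribution. The power figures below use d = 1.10, the effect for which 14 per group gives 80%.

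**Standard error.** With unit SD, the unadjusted standard error is √(2/14) = 0.378. Under full stratum balance the true value is 0.378 × √(1 − R²), which is 0.359 at R² = 0.10. In simulation the mean computed standard error was 0.376 and the true SD of the arm difference 0.360.

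**Type I error.** In large samples the unadjusted test has size 2[1 − Φ(1.96/√(1 − R²))]. At R² = 0.10 this is 2[1 − Φ(2.066)] = 3.9%. Simulation used 28 women, stratified permuted blocks of four and 8,000 null runs, so the simulation error at 5% is √(0.05 × 0.95/8000) = 0.24 points.

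| Assumed R² | t-test, formula | t-test, simulated | Mann-Whitney, simulated | Strata in model, simulated |
|---|---|---|---|---|
| 0 | 5.0% | 5.0% | 4.7% | 5.1% |
| 0.10 | 3.9% | 3.8% | 3.5% | 4.9% |
| 0.20 | 2.8% | 3.2% | 3.0% | 5.1% |
| 0.30 | 1.9% | 2.4% | 2.1% | 5.4% |
| 0.50 | 0.6% | 1.0% | 0.9% | 5.1% |

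With the same blocks but no stratification, the t-test stays at 5.0 to 5.2%. The shortfall therefore comes from the mismatch between design and test.

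**Power at d = 1.10** (4,000 runs; simulation error about 0.6 points):

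| Assumed R² | t-test | Strata in model |
|---|---|---|
| 0 | 80% | 79% |
| 0.10 | 80% | 82% |
| 0.20 | 82% | 87% |
| 0.30 | 83% | 92% |
| 0.50 | 86% | 98% |

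A separate simulation at R² = 0.10 and 0.25 gave type I errors of 4.0% and 2.7%, with power of 81% against 83% and 83% against 90%. Those are differences of 2 and 7 points.

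**Group-by-time contrast.** If the strata only shift a woman's overall level, the shift cancels in the change from baseline, and this test runs at 4.9 to 5.1%. If instead the severity stratum is the baseline score split in two, the stratum predicts change through regression to the mean. For baseline-outcome correlations of 0.3, 0.5 and 0.7, the change test then runs at 3.1%, 3.9% and 4.1%, and the post-treatment t-test at 4.3%, 3.5% and 2.0%. Adding the strata returns the post-treatment test to 4.9 to 5.2%.

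**The case against.** The strongest objection is to the premise. Only one line mentions strata, and the two other descriptions of the same randomisation do not. The Study Design text also puts assignment before the questionnaire that records age and before ICIQ-FLUTS. Stratifying would need an earlier source, such as the urologist's records, and none is named. This stands, and it makes the point conditional: without stratification the unadjusted tests run at 5%.

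A reader might infer that every planned between-group test runs below 5%. The documents do not support that. The group-by-time contrast holds its level when strata shift level only. In one run of that setting, with an assumed within-patient correlation of 0.5, it had power of 83.5% and 89.5% at R² = 0.10 and 0.25, about the same as the stratum-adjusted model (83.2% and 89.1%).

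A reader might also infer that power drops below plan. It does not: apart from simulation error, the t-test's power starts at 80% and rises with R². What is lost is a possible gain. The Mann-Whitney test starts lower, at 76% for this normally distributed effect, but that comes from using ranks and not from the strata.

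The prognostic link is also unproven. The Introduction says that prevalence rises with age, which does not show that age predicts post-treatment Qmax, PVR, voiding time or PGIC among affected women. For ICIQ-FLUTS, adjusting for severity may largely coincide with adjusting for the endpoint's own baseline. Both limits stand.

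A statistical analysis plan could add adjustment. The protocol, however, does not leave the tests open: it names unadjusted ones, and they do not match the stratification it states.

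**Conclusion.** The point holds as a conditional efficiency issue. If randomisation is stratified as stated and the strata are prognostic, the per-visit t-test and Mann-Whitney comparisons are conservative. The t-test's type I error is about 4.0% at R² = 0.10 and 2.7% at R² = 0.25, and it forgoes roughly 2 to 7 points of power against a matching adjusted analysis. These sizes rest on the assumed R² and the assumed 2×2 strata. At R² = 0 there is no error and no gain. The case is most plausible for ICIQ-FLUTS and unsupported by the protocol for the other endpoints. The disagreement over whether randomisation is stratified at all has to be settled first.

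**What to change.** 1. Reconcile the Study Design text and the first Randomization and Blinding list with section 2. Randomization and Blinding. If stratification is kept, define the severity measure and the cut-points, and name a source for both factors that is available before assignment.
2. If it is kept, replace the per-visit between-group tests in Statistical Analysis with a linear model containing treatment and the two stratification factors as used at randomisation. Age may be entered as continuous; the simulations used two binary factors, so that variant was not itself checked. For PGIC, which has no baseline, use a stratified rank (van Elteren) test or an ordinal model with the same factors.
3. If stratification is dropped, the standard-error problem disappears and covariate adjustment becomes an optional efficiency gain.

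The cost is a change of wording with no new measurement, since age and ICIQ-FLUTS are already planned data items; only their timing may need to move if they define the strata. The adjusted model uses two of the 26 residual degrees of freedom, a loss of about 1 power point or less if the factors prove unrelated to outcome.

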## **Summary of Methodology and Analysis**

### **Study Design**

Following ethical approval, a non-probability convenience sampling method will be employed. A urologist will evaluate patients with voiding dysfunction through:

- **Clinical history** (symptom assessment)
- **Neurological examination** (anal tone, voluntary anal control, genital/limb reflexes, sensory evaluation)
- **Urodynamic tests** (cystometry for detrusor pressure, uroflowmetry and pre-/post-void ultrasound to classify voiding dysfunction)

Eligible patients will complete a 3-day voiding diary (recording fluid intake, voiding frequency, and urinary patterns). They will then be referred to the physiotherapy clinic of rehabilitation faculty of Iran university of medical science with all of medical records. The urologist will remain blinded to group allocation. At the physiotherapy clinic, all participants will first receive a comprehensive explanation of the entire procedure and the purpose of the study. Then, individual informed consent forms will be obtained from each participant. Patients will be informed that there are two treatment groups, and except for the method of applying the interferential electrical current, all treatments in both groups are similar. Group assignment will be completely random, with an equal chance of being placed in either group. They will also be assured that if significant improvements are observed at the end of the study, the treatment received by the other group will be fully provided to them.

A completed 3-day urinary diary will be collected from each patient, and from this data, the frequency of bathroom visits within 24 hours will be extracted. Using a computerized random number list, patients will then be randomly assigned to either the treatment or control group in a 1:1 ratio, using blocks of four.

Next, a self-developed questionnaire collecting personal information such as age, height, and weight will be completed by all patients in both groups at the beginning of the first session. Afterward, all patients will receive the Persian versions of the female lower urinary tract symptom (FLUTS-ICIQ) and pelvic floor distress inventory-20 (PFDI-20) questionnaires to score the severity of their lower urinary tract symptoms and pelvic floor symptoms, respectively.

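### Randomisation is said to be stratified by age and symptom severity, but the protocol defines no strata and places its severity questionnaires after assignment

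*Protocol*

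**What the plan says.** The protocol describes the randomisation in three places.

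- **Study Design** (under Summary of Methodology and Analysis): "patients will then be randomly assigned to either the treatment or control group in a 1:1 ratio, using blocks of four". No strata are named.
- **Randomization and Blinding** (same summary): "computer-generated block randomization (block size = 4", again at 1:1 and without strata. Allocation is kept in sealed opaque envelopes until treatment starts. The therapist is unblinded; the urologist who assesses outcome is blinded.
- **2. Randomization and Blinding** (later, numbered section): "Computer-generated block randomization (1:1 ratio, block size=4", followed by "Stratified by age and symptom severity". It does not say how severity is measured, where the cut-points lie or how many strata there are.

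Study Design also fixes the order at the physiotherapy clinic. Consent comes first, then collection of the diary, then assignment. After assignment: "Next, a self-developed questionnaire collecting personal information such as age, height, and weight will be completed by all patients in both groups". Then: "Afterward, all patients will receive the Persian versions of the female lower urinary tract symptom (FLUTS-ICIQ", given together with PFDI-20, to score symptom severity.

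Under Variables, the severity of lower urinary tract symptoms is defined operationally by ICIQ-FLUTS. Under 4. Outcome Measures, ICIQ-FLUTS is a primary endpoint.

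**The concern.** A stratified list can be used only if the patient's stratum is known when the next allocation is drawn. Here the severity scores come after that moment, and nothing collected earlier is named as the stratifying measure. Whoever prepares the list cannot build it from the protocol, and whoever draws the envelope cannot tell which stratum to draw from.

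Two things are at stake. First, the protocol promises balance on age and severity that its own procedure does not deliver. Second, the baseline of a patient-reported primary endpoint is placed after assignment, in a clinic where one person will know the arm. The Statistical Analysis section uses baseline as one of the time points in the repeated-measures comparison, so any influence of the arm on baseline scores would enter the group comparison over time.

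**Working it through.** This is mainly a check of order and consistency, and the protocol gives no figure on this point to reproduce.

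**Step 1: what is known at assignment.** The order in Study Design, set against the two stratification factors:

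1. Urology screening: history and symptom assessment, urodynamics, ultrasound. This is symptom information, but no severity score is named.
2. Consent and collection of the 3-day diary, from which 24-hour frequency is extracted. This is not called severity.
3. Assignment.
4. Form recording age, height and weight.
5. ICIQ-FLUTS and PFDI-20.

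Severity as the protocol defines it (ICIQ-FLUTS) appears at step 5, two steps after it is needed. The study's own record of age appears at step 4, although age is probably in the medical records sent with the patient.

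**Step 2: do the three descriptions agree?** All give 1:1 and blocks of four. One adds strata; two are silent. None gives a measure or cut-points.

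**Step 3: does another section settle the order?** Assessment Timeline places baseline before treatment. That is not the same as before randomisation, so it does not.

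**Step 4: what stratification would do at this size.** Sample Size Calculation Method gives 14 per group, so 2 × 14 = 28 patients. The number of strata is not stated, so a range is assumed. In 40,000 simulated trials per setting, each patient fell into one of K equally likely strata, with blocks of four within each stratum.

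| Assumed strata K | Mean patients per stratum (28/K) | Mean strata ending mid-block | Mean difference between arms | Trials with a difference of 4 or more |
|---|---|---|---|---|
| 1 | 28 | 0 | 0 | 0% |
| 4 (2 × 2) | 7.0 | 3.0 | 1.3 | 8% |
| 6 | 4.7 | 4.5 | 1.7 | 16% |
| 9 (3 × 3) | 3.1 | 6.9 | 2.1 | 27% |

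Without strata, 28/4 = 7 complete blocks give exactly 14:14. A difference of 4 is a 16:12 split.

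**Step 5: what a 16:12 split costs.** Information relative to 14:14 is 4 × 16 × 12 / 28² = 768/784 = 0.98. The loss is about 2%, so unequal arms are a minor matter. The table shows only that several strata are hard to support with 28 patients.

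**The case against.** Several stronger readings are tempting, and the protocol does not support them.

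- **That stratification is impossible.** The numbered section says symptom severity without naming ICIQ-FLUTS. The urologist's assessment, flow rate, residual volume and diary frequency all exist before assignment, and Problem Statement treats residual volume and daytime frequency as key symptoms to evaluate. Any of these could define a stratum. This stands: the scheme fails only as sequenced and defined, and naming such a measure with a cut-point would repair it.
- **That two sections describe unstratified randomisation.** They are silent on strata, which is weaker than a contradiction. The conflict between the claimed strata and the order of events does not depend on them.
- **That baseline scores are biased by knowledge of the arm.** The envelopes conceal allocation until treatment begins, and the forms are completed at the start of the first session, so the forms may in practice precede opening. Patients also fill in the questionnaires themselves and are blinded by a sham. This largely stands. What remains is that Study Design writes assignment first, and no section says that the envelope stays closed until the forms are complete.
- **That the fixed block size compromises the trial.** For a single unstratified list, the six possible blocks of four contain 8 forced assignments in total, so 8/6 = 1.33 per block and 7 × 1.33 = about 9 of 28. Exploiting this needs someone who tracks the sequence and can also influence entry. A blinded urologist judges eligibility, and no section says that the therapist controls entry. A fixed block of four is a design preference and not an error in this document.
- **That the Statistical Analysis section wrongly omits the stratification factors.** Covariate adjustment may properly sit in a statistical analysis plan that is not shown. It is relevant to the repair but is not a defect here.

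**Conclusion.** The point holds in limited form. The protocol claims stratification by age and symptom severity, gives no strata, and orders events so that its severity questionnaires and its age form follow assignment. As written, the stratified scheme cannot be operated. The baseline of a primary endpoint is also written as falling after assignment, with only partial protection from the envelopes.

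The consequence is moderate. If the strata are simply not applied, concealed 1:1 permuted blocks remain a valid randomisation and balance on age and severity holds in expectation. No estimate is invalidated. The simulated imbalances rest on an assumed number of equally likely strata and are illustrative; the conclusion does not need them.

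This should be fixed, preferably before the first patient is assigned, because the order of baseline and assignment cannot be repaired afterwards.

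**What to change.** 1. In Study Design, move the age form, ICIQ-FLUTS and PFDI-20 to after consent and before the envelope is opened, and say explicitly that the envelope stays closed until they are complete.
2. State one scheme, in the same terms, in Study Design and in both randomisation sections. Choose one:
   - **Drop stratification** (simplest with 28 patients) and adjust the analysis for baseline score and age.
   - **Keep one binary severity stratum**, from a named measure available before assignment with a stated cut-point, and include that stratum in the analysis.
3. Varying the block size is optional.

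The cost is a reordering of forms at an existing visit, a new allocation list if a stratum is kept, and a few sentences of protocol text. No patients, visits or procedures are added. What is given up is the present claim of stratification on two factors, which is either withdrawn or narrowed.
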